**DISCONTINUATION AND WITHDRAWAL**

**7.1. Discontinuation of study intervention**

In the exceptional event the patient develops hypotension requiring therapy, apnea, or another adverse event reasonably attributable to Mg and the ED physician feels that the experimental therapy cannot be safely continued, the experimental treatment will be stopped and appropriate treatment given. Hypotension will be defined as systolic blood pressure <70 mm Hg +(age in years x2) in children 2-10 years old and as <90 mm Hg in those

>10 years old.

Lack of clinical improvement/deterioration after experimental therapy will be treated with administration of supplemental oxygen (if needed) and further inhaled salbutamol ± ipratropium treatments. Hypotension after experimental therapy will be treated with supplemental IV fluids/other measures, as per usual clinical practice. Neither of these scenarios apply to discontinuation of study intervention.

**7.2. Withdrawal from the study**

Participants are free to withdraw from participation of this study at any time upon request. An Investigator may discontinue or withdraw a participant from this study for the following reasons:

•

Withdrawal of informed consent (participant or parent/guardian withdraw for any reason)

•

If the participant’s blood pressure drops below the 5th percentile during the experimental infusion (this needs to be confirmed with manual BP measurement) and the treating physician feels that treatment is required,

Version Date: June 25, 2025 (v3.0)

Page **22** of **54**

[figure not shown]

**MAGICIAN** Clinical Trial Protocol

experimental infusion will be stopped but the child will remain in the study and study allocation will remain blinded. Participants who develop hypotension or receive open-label IVMg during the 180-minute observational period will also remain in the study without unblinding. Participants whose treatment assignment has been unblinded will also remain in the study.

**7.3. Lost To Follow-Up**

We anticipate virtually no loss to follow-up for the primary outcome because the primary endpoint will happen in the ED. Participants discharged home from the ED will be contacted via email or phone (as per the preference of the family) 72 hours after discharged for a follow-up survey. The site will make every effort to contact the participant daily up to 7-days after discharge.

If the participant is unable to be reached via phone or email (their preferred method of contact) within 7 days after discharge, we will consider them lost to follow-up for this secondary outcome. They will not be withdrawn from the study, we will record in the study database that we were unable to contact participant for the final study time point.

**8.**

**STUDY ASSESSMENTS AND PROCEDURES**

**8.1. Assessments**

The schedule of activities is provided in section 1.3 (SoA).

All relevant data will be captured on paper or electronic case report forms (eCRFs) in accordance with the eCRF completion guidelines.

**8.1.1.**

**Standard of Initial Asthma Care**

When a potential participant arrives in the ED with asthma/wheezing, the Standard of Care (SOC) for this population is for the triage nurse to take an arrival PRAM score, followed by administration of systemic corticosteroids, and 3 treatments with inhaled salbutamol and ipratropium over the course of approximately 1 hour.

**8.1.2.**

**Screening**

The study team will pre-screen all potential participants who arrive at the ED. The study nurse may be contacted if a participant is identified with a PRAM ≥ 5 after the first inhalation, if the child had no past co-morbidities, and had at least one past wheezing episode.

After approximately 1 hour of SOC, the study nurse will approach participant to discuss the study and measure an eligibility PRAM score. If the participant is

Version Date: June 25, 2025 (v3.0)

Page **23** of **54**

[figure not shown]

**MAGICIAN** Clinical Trial Protocol

eligible, they will screen all inclusion/exclusion, obtain informed consent, obtain history and demographics information.

**8.1.3.**

**Treatment Period**

The ED staff or study nurse, may use a topical anesthetic to start an IV if that is the practice at a given site. Prior to experimental therapy, they may also infuse IV Normal Saline bolus, according to site routine practices. The experimental infusion will last approximately 30 minutes. The study nurse will perform activities outlined in Section 1.3 (SoA) during this period.

**8.1.4.**

**Follow-Up**

Participants will receive a follow-up phone call or email (they may state their preference) 72 hours after they are discharged from the ED from the study team.

The study team may attempt to contact participants up to 7 days after discharge to answer the follow-up survey.

If the participant was admitted to the hospital at their index ED visit, they will not be contacted for the follow-up survey.

**9.**

**STATISTICAL CONSIDERATIONS**

**9.1. Sample size**

Sample size is based on the assessment of the PRAM change in the IVMg vs the control group and we *conservatively* aim for an inter-group PRAM difference in change of ≥1.0 point (SD 2.5), based on the following evidence. Children 1-17 years old with a baseline PRAM ≥4 points had a median PRAM change of 3 points if discharged vs.1 point if admitted.25 In a PRAM validation study of children with moderate dyspnea anchored against expert physician-perceived clinical improvement a PRAM change of 1.5 (SD 2.3) was seen for children judged clinically improved vs. 0.0 (SD 2.2) for those unchanged.67 When compared to a change in respiratory rate percentile, a PRAM change of 1.1 (SD 2.7) was seen in the improved patients vs.0.3 (SD 2.2) in those unimproved.67 Based on this evidence, the investigators agree that a minimally clinically significant difference in PRAM changes between groups is 1 point. Although the study non- compliance and loss to follow-up rates in MAGNUM were both 0%, we conservatively assume that the non-compliance (crossover) with allocated therapy and the follow up loss may be as high as 5% and 1%, respectively. Based on these parameters, a study sample of 192 children (96 per group) provides 80% power with a two-sided significance level 0.05. Accounting for the randomization factors of site and age, a sample of 192 children obtained by recruiting in 12 strata (2 ages x 6 sites) with a similar number of children per strata, a significance level of 0.05 and an intracluster correlation coefficient of 0.05, achieves 80% power to detect PRAM difference in change of 1.0 (SD 2.3) based on a mixed-model analysis.

Version Date: June 25, 2025 (v3.0)

Page **24** of **54**

[figure not shown]

**MAGICIAN** Clinical Trial Protocol

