Trial results will impact care regardless of whether an association is found. If IVMg is found to decrease respiratory distress, we will use knowledge translation (KT) to implement *routine and early* IVMg therapy for refractory asthma. A negative result will be followed by de-implementation strategies to cease the use of IVMg for refractory asthma which may also lead to cost savings: IVMg therapy is personnel- intensive, requires an IV which may not be necessary in moderate-severe asthma, may cause hypotension,10 and as such greatly augments the odds of hospitalization.11,23

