**5.3. Strategies For Recruitment and Retention**

We expect 6 Canadian Hospitals to participate in this study. The anticipated study duration is approximately 38 months. We anticipate an 8-month pre-enrollment period, patient recruitment will occur for approximately 26 months, and an estimated 4-month post-enrollment period.

The target sample size is 192 participants. We anticipate an accrual rate of 7-8 participants a month in Emergency Departments (ED) across all sites.

Children presenting to the collaborating EDs who meet eligibility criteria will be approached for enrollment when the research nurses are on duty/on call (days and

Version Date: June 25, 2025 (v3.0)

Page **16** of **54**

[figure not shown]

**MAGICIAN** Clinical Trial Protocol

evenings). Participating sites have research assistants in the ED who will pre-screen potentially eligible patients and ensure the miss rate is kept to a minimum.

As per our previous MAGNUM trial with a similar design, we estimate that only 15% of screened patients will participate: 75% will be ineligible and 50% of the remaining will decline consent or not join for other reasons.3 We shall adopt the MAGNUM enrollment schedule, with coverage by on-call research nurses, to enroll 192 patients with full data across 6 sites in approximately 26 months. This is achievable given that MAGNUM used the same eligibility criteria and entry asthma severity and randomized 729 children with full data at 7 centers in 5 years (21 patients/year/site). Thus, we anticipate annual enrollment of 109 eligible consenting children with full data based on annual asthma ED presentations **(Appendix F)** and a conservative estimate of 30% weekly hours coverage, 25% eligibility, 50% of those eligible not participating for refusals/other reasons, 5% non-compliance with intervention (crossover) and 1% loss to follow up.

**6.**

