**9.13.**

**Adherence**

This is unlikely to be a problem since intervention delivery will be given in the ED. The experimental period is short and IV administration guarantees medication delivery.

Conservatively, we assume a 5% crossover between groups; the sample size has been adjusted accordingly.

Version Date: June 25, 2025 (v3.0)

Page **28** of **54**

[figure not shown]

**MAGICIAN** Clinical Trial Protocol

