**Results:** Among 818 randomized patients (median age, 5 years; 63%males), 816 completed the trial (409 received magnesium; 407placebo). A total of 178 of the 409 children who received magnesium (43.5%) were hospitalized vs 194 of the 407 who received placebo (47.7%) (difference, −4.2%; absolute risk difference 95%[exact] CI, −11% to 2.8%]; *P* = .26).

There were no significant between-group differences in changes from baseline to 240

minutes in PRAM score (difference of changes, 0.14 points [95% CI, −0.23 to 0.50]; *P* = .46);

respiratory rate (0.17 breaths/min [95%CI, −1.32 to 1.67]; *P* = .82); oxygen saturation

Version Date: June 25, 2025 (v3.0)

Page **39** of **54**

[figure not shown]

**MAGICIAN** Clinical Trial Protocol

(−0.04% [95%CI, −0.53%to 0.46%]; *P* = .88); systolic blood pressure (0.78mmHg [95%

CI, −1.48 to 3.03]; *P* = .50); or mean number of additional albuterol treatments (magnesium: 1.49, placebo: 1.59; risk ratio, 0.94 [95%CI, 0.79 to 1.11]; *P* = .47). Nausea/vomiting or sore throat/nose occurred in 17 of the 409 children who received magnesium (4%) and 5 of the 407 who received placebo (1%).

**Conclusions and Relevance:** Among children with refractory acute asthma in the emergency department, nebulized magnesium with albuterol, compared with placebo with

albuterol did not significantly decrease the hospitalization rate for asthma within 24 hours. The findings do not support use of nebulized magnesium with albuterol among children with refractory acute asthma.

Version Date: June 25, 2025 (v3.0)

Page **40** of **54**

[figure not shown]

**MAGICIAN** Clinical Trial Protocol

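### The 80% power stated for 192 children does not follow from the inputs listed with it (difference 1.0, SD 2.5, 5% crossover, 1% loss); those inputs give about 74%, and 192 fits SD 2.3 instead

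*Protocol*

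**What the plan says.** Section 9.1 of the protocol makes two power statements for the same 192 children.

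- **First statement.** The target is an "inter-group PRAM difference in change of ≥1.0 point (SD 2.5"). The section then assumes that "the non-compliance (crossover) with allocated therapy and the follow up loss may be as high as 5% and 1%, respectively". On those parameters it states that "a study sample of 192 children (96 per group) provides 80% power with a two-sided significance level 0.05".
- **Second statement.** Allowing for site and age as 12 similar-sized strata with an intracluster correlation of 0.05, the same 192 "achieves 80% power to detect PRAM difference in change of 1.0 (SD 2.3) based on a mixed-model analysis".

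Section 9.13 (Adherence) confirms that crossover is meant to be inside the sample size: "Conservatively, we assume a 5% crossover between groups; the sample size has been adjusted accordingly".

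Section 9.5 plans an intention-to-treat analysis. Section 9.6 compares the groups with Student's t-test on the change in PRAM at 120 minutes, and adds a multiple regression adjusted for site and age.

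Section 5.3 gives 192 as the target sample size, and later plans "to enroll 192 patients with full data across 6 sites in approximately 26 months".

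**The concern.** Two different SDs, 2.5 and 2.3, are attached to one sample size and one power figure, with no reason given for the change. At SD 2.5, 192 is already slightly short of 80% with perfect compliance and follow-up, so nothing is left for the crossover and loss that the text says are included. Under intention-to-treat, children who cross over stay in their allocated arm and dilute the difference.

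The stated power tells readers how often the trial would miss a true benefit of 1.0 point, which Section 9.1 calls the minimal clinically significant difference. At the first statement's own inputs that miss rate is about 26%, not 20%.

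**Working it through.** **Inputs.** Difference 1.0; SD 2.5 or 2.3; 96 per group; two-sided 0.05; 5% crossover; 1% loss (all Section 9.1). Allocation is 1:1 (Section 6.5). The test is a two-sample t-test under intention-to-treat (Sections 9.5 and 9.6).

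**Formula.** Exact noncentral t with n per group: λ = δ / (SD × √(2/n)), df = 2n − 2, power = P(|T| > t₀.₉₇₅).

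**Allowances.** Loss: 96 × 0.99 = 95.04 per group. Crossover: δ = 0.95 if 5% cross over in total or in one arm; δ = 0.90 if 5% cross over in each arm. The protocol does not say which it means.

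**Step 1. Trying to reproduce 80% at SD 2.5**

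| Handling of allowances | n per group | δ | λ | Power |
|---|---|---|---|---|
| None | 96 | 1.00 | 1/(2.5 × √(2/96)) = 2.771 | 78.7% |
| 1% loss only | 95.04 | 1.00 | 2.757 | 78.3% |
| Crossovers and losses removed | 96 × 0.94 = 90.24 | 1.00 | 2.687 | 76.2% |
| 1% loss, dilution to 0.95 | 95.04 | 0.95 | 2.620 | 74.1% |
| 1% loss, dilution to 0.90 | 95.04 | 0.90 | 2.482 | 69.5% |

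The normal approximation gives 79.1% in the first row and 74.5% in the fourth, so the method is not the cause. No two-sided reading that includes both allowances reaches 80%. The final-analysis level of 0.0492 (Section 9.10) lowers each figure by only about 0.2 points.

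For 80% at SD 2.5 the t-test needs 100 per group before any allowance. With δ = 0.95 it needs 110 per group, and 110/0.99 = 111.1.

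**Step 2. The same check at SD 2.3**

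- No allowances: λ = 1/(2.3 × √(2/96)) = 3.012, power 85.0%.
- 1% loss and dilution to 0.95: λ = 2.847, power 80.9%.
- Sample size: 85 per group unadjusted, and 85/(0.95² × 0.99) = 95.1, which rounds up to 96 per group, or 192.

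So 192, 80% power, 5% crossover and 1% loss agree with one another at SD 2.3 and not at SD 2.5.

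**Step 3. The second power statement**

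Children are randomised within site and age strata, so variation between strata is removed from the treatment comparison and does not inflate it. Reading SD 2.3 as the total SD, the within-stratum SD is 2.3 × √(1 − 0.05) = 2.24.

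- 96 per group, δ = 1.0: 86.8%.
- 95.04 per group, δ = 0.95: 82.8%.
- If 2.3 is instead the residual SD: 85.0% before the allowances and 80.9% after.

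The sentence's listed inputs therefore give 85% to 87%. It comes near 80% only when the crossover and loss, which it does not mention, are added.

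**Step 4. Detectable difference at SD 2.5**

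With 95.04 per group, 80% power needs a difference of 1.021 in the groups as analysed. Dividing by 0.95 gives a true difference of 1.075, or about 1.08 points.

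**The case against.** The strongest reply is that the trial may have the power it claims. SD 2.3 is printed in the same paragraph, and 192 is exactly what SD 2.3 with the stated allowances requires. The SDs quoted there as evidence (2.3, 2.2, 2.7, 2.2) have a root mean square of about 2.36, which gives about 79%. This stands. A reader might infer that the trial is underpowered, but the documents support only that the stated figure and its stated SD do not match.

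Other points that stand:

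- **The lowest figure is a worst case.** About 69% needs 5% crossover in each arm. Section 9.1 calls 5% conservative against 0% in the earlier trial, and the route described, open-label magnesium, would mainly affect placebo children.
- **Without allowances the gap is small.** 78.7% against 80% is close to rounding. The failure is that nothing remains for the allowances.
- **The second statement has some basis.** Section 9.6 does plan a regression adjusted for site and age. It is still not a mixed model, and the inputs still do not give 80%.

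Two further inferences go beyond the documents:

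- **A larger SD from the earlier trial.** Appendix A reports a "difference of changes, 0.14 points [95% CI, −0.23 to 0.50"]. The half-width is 0.365; 0.365/1.96 = 0.186; and 0.186/√(1/409 + 1/407) = 2.66. That is at 240 minutes, in a trial of nebulised magnesium, and assumes an unadjusted interval. It does not show that 2.5 or 2.3 is wrong at 120 minutes.
- **A rule for interpreting a null result.** Section 2.1 says that "A negative result will be followed by de-implementation strategies to cease the use of IVMg for refractory asthma". This makes the power figure consequential, but it is rationale text and not an analysis rule. Adding an interval-based criterion would not repair the arithmetic.

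Reading 192 as children with full data does not rescue the figure either. It conflicts with 192 as the target sample size, and with no loss at all, dilution to 0.95 still leaves 74.5%.

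**Conclusion.** The first power statement in Section 9.1 is wrong for its own inputs. At SD 2.5 with the stated allowances, power is about 74%, some 6 points below the stated 80%, with a range of 69% to 76% depending on how crossover is counted. The 74% assumes intention-to-treat dilution to 0.95 and 1% loss.

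The shortfall disappears (about 81%) if SD 2.3 is the intended value, so the firm conclusion is a contradiction that must be resolved, not a proven lack of power. The second statement does not resolve it: it changes the SD without explanation, names an analysis that is not the planned primary test, and reports 80% where its inputs give about 87% with SD 2.3 read as the total SD (83% after the allowances). Section 5.3 also leaves open whether 192 counts randomised or evaluable children.

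**What to change.** Keep 192 and revise Section 9.1:

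1. Use one SD throughout and justify it.
2. State whether 192 is the number randomised or the number evaluable, and make Section 5.3 agree.
3. State whether the 5% crossover is in total or in each arm, and restate the power to match. With dilution to 0.95 and 1% loss this is about 74% at SD 2.5 (80% power for a difference of about 1.08), or about 81% at SD 2.3.
4. Delete the intracluster-correlation sentence, or recompute it for the planned t-test or the stratification-adjusted regression.

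The cost is protocol wording. No extra children are needed. The only downside is a less favourable stated power if SD 2.5 is kept.

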**9.2. The primary outcome measure**

The primary outcome measure will be the PRAM score,25,53 measured at 30, 60, 120 and 180 minutes post intervention, with the 120 minute measurement as the primary end- point. PRAM is the best tool to ascertain clinical response in this trial. It is routinely used in pediatric EDs across Canada and abroad to guide asthma therapy and will: a) help identify eligible candidates, b) measure the incremental benefit of IVMg across sites, c) promote acceptance of trial results by the end-users, d) provide greater sensitivity to change than spirometry, and e) facilitate implementation of findings in Canada and beyond.

Two ED studies (N=200) of children with moderate-severe acute asthma confirmed that the PRAM score at 3 hours post initial management accurately predicted hospitalization/long ED stay (AUC 0.85 to 0.88, OR 2.0) as well as clinical improvement (our primary end-point).58,65 This time point also corresponds to 4 hours post initial CS therapy when CS is expected to act and hospitalization decisions are usually made. PRAM is a 12-point instrument validated in children 1-17 years old with acute asthma in the ED exhibiting the most comprehensive measurement properties of all pediatric acute asthma scores,54 which was successfully used as an outcome in major trials.3,55 PRAM is the only pediatric acute asthma score developed for pre-schoolers by criterion (oscillometry) and construct (physician severity appraisal) validity.25,53 PRAM also demonstrates good discrimination and responsiveness to change: a construct- validation (hospitalization) in 800 children aged 1-17 years (oscillometry and physician appraisal) showed good internal consistency (Cronbach α 0.7), responsiveness (Guyatt responsiveness index 0.7), and inter-rater reliability across ages.25,53 PRAM is one of two scores that performed best in validation, responsiveness, and reliability in the two systematic reviews.54,66 Two prospective validation studies compared the psychometric properties of the highest-rated clinical scores in 50 children.67,68 One found PRAM as one of two most valid (construct and content-wise) scores of 36 dyspnea scores. The inter-rater reliability was modest, because of no rating of the auscultation and palpation criteria, which represented 3 of 5 items.67 The second study rated PRAM as second-best for predicting hospitalization (AUC 0.89).68 Because the raters were not PRAM-trained, the inter-rater reliability was lower than in the primary studies (weighted kappa 0.50): this will be remedied by a mandatory participation in an online training module57 by all research nurses. While PRAM detected significant and meaningful changes in ED treatment from baseline to 4 hours in school-aged children, spirometry did not, suggesting a higher PRAM sensitivity to change.69 Unlike spirometry, PRAM will allow inclusion of preschoolers who represent 60% of asthma visits to pediatric EDs and 40% of the school-aged children unable to perform spirometry.56

*We considered but rejected using hospitalization as the primary outcome as it would likely artificially attenuate inter-group difference and mask a true difference in clinical improvement.* Hospitalization is a subjective decision influenced by asthma severity, hospital policy and provider risk-tolerance. Further, major confounding by indication is

Version Date: June 25, 2025 (v3.0)

Page **25** of **54**

[figure not shown]

**MAGICIAN** Clinical Trial Protocol

likely.11,23 Finally, a meaningful PRAM effect size would provide a compelling reason for *routine early use* of IVMg, regardless of hospitalization, while hospitalization is irrelevant with a null or negative result.

The 120-minute time point includes the initial asthma therapy (one hour), subsequent period involving eligibility confirmation, informed consent, IV placement and pre- hydration (approximately one hour) and the two-hour period after the start of experimental therapy. Because corticosteroids are typically given at the start of the initial therapy, the 120-minute point will occur approximately 4 hours post corticosteroids when most of the improvement after corticosteroids occurs (Alnaji et al, Acad Emerg Med 2014).

**9.3. Secondary outcome measures**

The two study groups will also be compared with respect to:

1. Hospitalization for asthma at the index ED visit.
2. Changes in PRAM, respiratory rate, heart rate, oxygen saturation and blood pressure from baseline (pre- intervention) to 30, 60, 120, and 180 min and also in blood pressure to 10 and 20 min post-intervention
3. Area under the receiver operating characteristic curve for the PRAM score changes at 30, 60, and 120 minutes.
4. PRAM denoting mild asthma (≤ 3 points is a widely accepted discharge criterion25) at 120 minutes
5. Hospitalization for asthma at any medical facility within 72 hours post- ED discharge.
6. Unscheduled asthma-related visits to any health care provider within 72 hours post- ED discharge.
7. Hospital length of stay.
8. Open label IVMg administration after the 120-minute measurement of the primary outcome.

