**1.2. Schema**

**Triage Registered Nurse (RN):** Arrival PRAM score (**see Appendix B (PRAM Score)**)

Moderate to severe disease:

Assessment by ED physician Systemic corticosteroids

Initial therapy with 3 treatments with salbutamol & ipratropium (as per site drug dosing and ipratropium indications) over about 1 hour

Study nurse notified

**Study Nurse measures eligibility PRAM at end of initial therapy, if ≥ 5:** assesses eligibility (If eligibility PRAM is < 5, subject is ineligible for study)

If eligible, **Study Nurse** obtains informed consent

IV start, infusion of IV Normal Saline (NS) bolus as per site standard of care

**Study Nurse** retrieves next appropriate randomized treatment kit from research fridge/pharmacy department

**ED/Study Nurse** infuses experimental solution over 30 minutes

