**Screening/Eligibility**

**Baseline (Pre-Intervention)** (Measurements completed as close to before giving intervention)

**Time Point 0** (administer intervention)

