**STUDY DESIGN**

**4.1. Overall Design and the Scientific Rationale for Study Design**

As mentioned above, previous RCTs of IV Mg in children are small and have methodologic limitations. The most recent systematic review (Griffiths, 2016) concludes there is equipoise about IV Mg benefit. More recent large IVMg studies cast doubt on Mg benefit but these have non-RCT designs. Therefore, we propose a 6-centre randomized, double-blind, placebo-controlled trial. Two groups will be compared: IVMg sulfate and IV0.9% saline placebo. After initial therapy with the systemic CSs routinely used for acute asthma management at a given site, 3 treatments with inhaled salbutamol and ipratropium (indications for ipratropium vary by site),52 eligible patients with PRAM ≥5 **(Appendix B: PRAM Score)** will receive a 30-minute IV infusion of 75 mg/kg of Mg sulfate (maximum 2.5 g) [experimental group] or an identical volume of 0.9% saline [control group]. Outcomes will be measured during the 180-minute observational period in the ED and at 72 hours post ED discharge. Primary outcome will be the PRAM score at 120 minutes after start of experimental therapy.

PRAM: PRAM is a validated 12-point asthma severity score53 which exhibits the most comprehensive measurement properties of all asthma scores54 and has been successfully used as an outcome in major trials.3,55 It is the only score with demonstrated criterion validity, using respiratory resistance as the gold standard.25,53 PRAM has been validated in both preschool and school-aged children in the ED with asthma and has strong association with admission.25 PRAM has inter-rater reliability above 70%25 and is adopted in all pediatric EDs in Canada. Most children treated for acute asthma are preschoolers56 who lack coordination to perform pulmonary function tests reliably. To maximize the accuracy of the PRAM measurement, all study nurses will complete online PRAM training module57 at https://enseignement.chusj.org/PRAM-En. We will use an eligibility cut-off of PRAM ≥ 5 post initial therapy as this is associated with clinically concerning respiratory distress requiring further intervention. PRAM ≥ 5 after one hour of initial care has high accuracy (AUC: 0.88) to predict hospitalization.58 Of the 215 children given IVMg in MAGNUM, 118 had PRAM 5, 41 PRAM 6, 35 PRAM 7 and 21 PRAM ≥8 prior to IV Mg.3

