**STUDY POPULATION**

**5.1. Inclusion criteria:**

1. Age 2.00-17.99 years (prior to 18th birthday),
2. Diagnosis of asthma, defined as an asthma or probable asthma diagnosis/asthma- like phenotype made by a physician (this includes ED physician) in a patient who in the opinion of the treating ED physician requires therapy for acute asthma in the ED (GINA asthma guidelines, 2024).59
3. Moderate-severe asthma after initial therapy with 3 treatments of inhaled salbutamol and ipratropium, defined as an eligibility PRAM ≥5, indicating a strong association with hospitalization.25

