**STUDY INTERVENTION**

**6.1. Study Intervention Description**

Previously healthy children 2.00-17.99 years of age with acute asthma will have PRAM routinely measured in triage, as per usual practice. Children presenting with a PRAM ≥ 5 will be considered potentially eligible and will receive oral dexamethasone, predniso(lo)ne or IV CS in triage/shortly thereafter. They will also receive three salbutamol and ipratropium inhalations61 via Metered Dose Inhaler/valved holding chamber approximately 20 minutes apart, with medication doses and ipratropium indications depending on local practice. If the PRAM is ≥ 5 after the first bronchodilator treatment and the child has no co-morbidities,62 a consent to approach for research will be obtained. At the conclusion of the 3 baseline inhalations, the research nurse will confirm eligibility, confirm the eligibility PRAM score, and obtain informed consent. A topical anesthetic may be used at the IV if that is the practice at a given site and IV line will be inserted. Participants may also receive an IV fluid bolus, as per site ED practice, prior to the experimental therapy, to improve hydration and prevent hypotension.

Thereafter, the trained and intervention-blinded study nurse will enter the patient eligibility data into the database, obtain the next study kit assigned to the appropriate age group (<6th birthday vs age 6 years and older) from the study fridge and enter the study kit number in the database. Master lists will be provided to all participating research pharmacies which will permit the preparation of the study kits according to the randomization schedule. Prior to the start of the experimental therapy, the study nurse will measure the patient’s Baseline PRAM, respiratory rate, heart rate, blood pressure and oxygen saturation.

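### The PRAM ≤3 outcome at 120 minutes takes no account of the pre-infusion Baseline PRAM, which carries no entry threshold; the effect is some dilution and lost precision, not bias

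*Protocol*

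**What the plan says.** **Entry.** Inclusion criterion 3 (Protocol 5.1) is "Moderate-severe asthma after initial therapy with 3 treatments of inhaled salbutamol and ipratropium, defined as an eligibility PRAM ≥5". The schema (1.2) places the reading: "Study Nurse measures eligibility PRAM at end of initial therapy, if ≥ 5".

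**Gap.** Section 9.2 describes what lies between initial therapy and the start of the infusion: "subsequent period involving eligibility confirmation, informed consent, IV placement and pre- hydration (approximately one hour".

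**Baseline.** Section 6.1 first has the nurse obtain the kit and enter its number. It then says: "Prior to the start of the experimental therapy, the study nurse will measure the patient’s Baseline PRAM". The schedule of activities (1.3) has a baseline column separate from screening, described as "Measurements completed as close to before giving intervention". No section attaches a threshold to this reading or says what happens if the score has fallen.

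**Outcome and analysis.** Section 9.3 item 4 is "PRAM denoting mild asthma (≤ 3 points is a widely accepted discharge criterion25) at 120 minutes", with no condition on baseline. Section 9.5 adopts intention to treat. Section 9.7 compares binary outcomes by chi-square, then by logistic regression adjusted for site and age. It calls the secondary analyses exploratory. Appendix E uses the same ≤3 threshold as treatment response, at 180 minutes.

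**The concern.** The objectives (1.1 and section 3) ask what proportion of children achieve mild status. A child who scores 5 at the eligibility reading and 3 just before the infusion has mild status before receiving anything. If still at ≤3 at 120 minutes, that child counts the same as one brought down from 7 by treatment.

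The two cut-offs are only two points apart, and the protocol's distribution from its earlier nebulised-magnesium trial (4.1) puts most children at the lower one: "118 had PRAM 5, 41 PRAM 6, 35 PRAM 7 and 21 PRAM ≥8 prior to IV Mg", so 118/215 = 55% at PRAM 5.

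At stake are the size and precision of the group difference in PRAM ≤3, and the meaning of treatment response in the economic analysis, which uses the same threshold. The primary analysis (9.6) uses change in PRAM and is not misclassified in this way, although a child at 3 before the infusion can improve by at most 3 points.

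**Working it through.** The protocol states no rate, effect size or power for PRAM ≤3, so there is no figure to reproduce. The question is how many children could be affected.

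**Inputs**
- Entry mix 118/41/35/21 at PRAM 5/6/7/8 (4.1; ≥8 taken as 8). As weights: 0.549, 0.191, 0.163, 0.098. These are pre-IVMg scores in the earlier trial, used as a proxy.
- SD of PRAM change in children judged unchanged: 2.2 (9.1).
- SDs of 1.3 and 1.8: assumptions.
- N = 192.

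**Step 1: at ≤3 at baseline, no true change.** For entry score k and reading-to-reading SD s, with rounding to whole points, P(≤3 | k) = Φ((3.5 − k)/s).

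For s = 2.2 this is 0.248, 0.128, 0.056 and 0.020 at k = 5, 6, 7, 8. Weighted: 0.549×0.248 + 0.191×0.128 + 0.163×0.056 + 0.098×0.020 = 0.171.

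**Step 2: at ≤3 at baseline and again at a later reading.** In the same model the two readings are independent given k, so each probability is squared. For s = 2.2: 0.549×0.248² + 0.191×0.128² + 0.163×0.056² + 0.098×0.020² = 0.037.

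| SD | ≤3 at baseline | of 192 | ≤3 at both | of 192 |
|---|---|---|---|---|
| 1.3 | 7.4% | 14 | 0.9% | 2 |
| 1.8 | 13.2% | 25 | 2.4% | 5 |
| 2.2 | 17.1% | 33 | 3.7% | 7 |

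Without true change, then, only 12% to 22% of the children at ≤3 at baseline are there again later (0.9/7.4 to 3.7/17.1).

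**Step 3: a model that allows for selection on a noisy reading.** Assume true scores N(5, SD 2), error SD s/√2, and entry on an observed score ≥5. The share at ≤3 at baseline is then about 4%, 9% and 12% for the three SDs. About 30% to 34% of those are at ≤3 again later, so roughly 0.04×0.30 ≈ 1% to 0.12×0.34 ≈ 4% at both.

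**Step 4: real improvement.** If the mean is 0.5 points lower at both readings (assumed), step 1 gives 13% to 23% at ≤3 at baseline and step 2 gives 2.7% to 6.6% at both. Further true improvement by 120 minutes would keep more of these children at ≤3, in both arms.

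**Step 5: dilution.** If a share f is at ≤3 beforehand and equally likely in both arms to be at ≤3 at 120 minutes, the risk difference is multiplied by (1 − f). Assume 35% vs 55% among the other children and 96 per arm:
- f = 0: 20 points, power 80%
- f = 5%: 19 points, power 75%
- f = 10%: 18 points, power 71%
- f = 20%: 16 points, power 61%

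This is a pessimistic illustration. It assumes treatment makes no difference to any child who starts at ≤3, whereas step 2 shows that many would rebound and could still benefit.

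**The case against.** **The endpoint is a status measure.** PRAM ≤3 is presented as a discharge criterion, and whether a child is dischargeable at 120 minutes means something whatever the baseline. Change from baseline is already the primary analysis and secondary item 2. This stands, and it is why the all-randomised comparison should stay as the main analysis.

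**The inputs are weak.** The SD of 2.2 comes from a validation study which, according to 9.2, had modest inter-rater reliability because auscultation and palpation items, 3 of the 5, were not rated. This trial trains its nurses in PRAM. The entry mix describes children whom physicians chose to treat with IVMg. The hour in 9.2 includes eligibility confirmation, so it is an upper limit on the gap. All of this stands.

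**Selection is stricter than one reading.** The pathway in 6.1 looks at PRAM ≥5 at presentation, after the first bronchodilator and at eligibility. If all three are required in the step 3 model, with a constant true state, the baseline share falls to about 1%, 3% and 5%. The formal criterion is still only the last reading, but the point supports the lower end of the range.

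**Covariates can be left to the analysis plan.** In general, yes. Here, however, 9.7 names the adjustment set for this model and leaves Baseline PRAM out.

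**A stronger inference to avoid.** A reader might conclude that every child at ≤3 before treatment is a responder whatever is given, so that up to 17% of the trial is predetermined. The documents do not support this: the child counts only if at ≤3 at 120 minutes as well, and in the no-change model most are not.

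**Conclusion.** The point holds in a limited form. The entry threshold need not hold at the pre-infusion baseline, and the PRAM ≤3 analysis ignores that baseline. The share affected is unknown. Under the stated assumptions it is about 4% to 17% at baseline and 1% to 4% at both readings when nothing truly changes; real improvement would raise both ranges, and selection on three readings would lower them.

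The consequence is some dilution and lost precision in an exploratory secondary outcome, and a blurred meaning of achieving mild status. A reader might infer bias between arms. That does not follow: assignment is randomised, the assessor is blinded and the baseline precedes the drug. Nor do the documents show that the entry rule is wrong.

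Two wording conflicts bear on the same reading. Section 6.1 describes Baseline PRAM after the kit has been obtained, while 9.8 has PRAM measured before randomisation. Section 3 names a pre-randomisation PRAM subgroup, while 9.11 calls it post-randomisation.

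**What to change.** 1. In 9.7, add the pre-infusion Baseline PRAM as a covariate in the logistic regression for PRAM ≤3 at 120 minutes, alongside site and age. The data are already collected. The gain depends on how strongly Baseline PRAM predicts the outcome: an illustrative simulation on assumed inputs moved power from about 79% to 86%, which shows direction rather than a forecast for this trial.
2. Keep the all-randomised intention-to-treat comparison as the main analysis, and report the number at PRAM ≤3 at baseline by arm.
3. Give the analysis restricted to Baseline PRAM >3 as a sensitivity analysis only, because it shrinks the denominator and answers a narrower question.
4. Reconcile 6.1 with 9.8 on when Baseline PRAM is taken relative to randomisation, and section 3 with 9.11 on which PRAM defines the subgroup.

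Items 1 to 4 cost wording and a few lines of output. Whether the entry threshold must be reconfirmed before a kit is assigned is for the sponsor to decide and state. Reconfirmation would mean that some consented children with an IV in place are not randomised, so it is a trade-off and not part of this recommendation.
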